## II.4. Study procedures

### III. Objectives and measurable assessment criteria

Objectives are divided into two parts as following:

#### III.1. Phase I

[figure not shown]

#### ✓ **Primary objectives**

To estimate:

- Hifu shootings **feasibility**,

↳ Through :

- 1) Ability to shoot :

- On the surface of the liver : in this case the hurt will start from the Glisson capsule and be extended to the subjacent parenchyma, and
- In DEPTH: In this case the hurt will be located in deeper parenchyma, at least 10 mm deeper than surface hurts.

- 2) The supplementary duration of intervention for 2 shootings given in minutes includes:
  - a. time to initialize the MD in operating room;
  - b. probe conditioning with acoustic coupling liquid;
  - c. time to define the target (x2) ;
  - d. time to deliver a shooting (x2).

The overtime caused must not exceed 30 minutes.

NB : Step a. and b. above-mentioned can be done in parallel to surgery. As far as they do not increase the duration of the surgical operation, they will not be taken into account. Same for the subsidiary research acts such as implanting marks.

- **Safety** using the MD,

↳ Through :

- 1) Capability to use the MD following requested asepsis procedures ,
- 2) No evidence of hurt on peripheral tissues (Glisson capsule on the opposite side of the HIFU shootings entrance area, retro-peritoneal, retro-hepatic tissues and diaphragm).

NB : it is possible that the Glisson capsule ultrasound hurts on the entrance area, that will be notified but not considered as a failure.

- HIFU shootings **tolerance**,

↳ Through: Ability to keep vital signs stable (hemodynamic, respiratory, body temperature) during shooting phase and the following 5 minutes.

 Hemodynamic vital signs : heart rate (HR), blood pressure (BP), heart flow (HF), by measuring the area under the curve on the Vigleo (N°3) monitor.

A significant alteration of vital signs will be defined as, at least, a 10% modification of one of these parameters compared to its value prior shootings.

✓ **Secondary objectives**

To determine :

- **Probe ergonomics** and feasibility of **area targeting**,
  - ↳ Through : Ability to adjust the probe position to different liver segments and patient physical structure. The aim is to be free to generate a HIFU hurt in at least 80 % of the total liver volume.
- Feasibility to set a mark (mark to estimate shootings accuracy in phase IIa-step 1),
  - ↳ Through : Possibility to set a stationary mark, at given depth, ecographically detectable,
- Feasibility to spot a specific vessel (used to estimate shootings targeting accuracy in phase IIa-step 2),
  - ↳ Through : Possibility to spot ecographically a previously Patent Blue or Methylene blue marked vessel.
- **Each step duration** to set the MD (initialization, conditioning, targeting, shooting – cf. supra),
  - ↳ Through : Mean duration to achieve each step expressed in minutes.
- Feasibility of real-time monitoring of the HIFU impact using an echograph combined with the MD,
  - ↳ Through : Possibility to locate HIFU hurt shape, to identify and to describe its outline (diameters, depth, volume etc.) during perioperative echography.
- Feasibility of **hurt early anatomopathological description** ,
  - ↳ Through : Possibility to locate HIFU hurt shape, to identify and to describe its limits (diameters, depth, volume, etc. – en mm) during anatomopathological analysis
  - NB: anatomopathological procedures will be standardized in this phase.
- Feasibility to **measure distance between the mark / marked vessel and the hurt limits** during anatomopathological analysis,
  - ↳ Through : Precise measure given in mm by the anatomopathologist.

### **III.2. Phase II**

---

 Respiratory vital signs : saturation of Peripheral O2 (SpO2) or partial pressure of oxygen (PAO2 – samples will be taken prior shootings and during the ending phase of evaluation, that is to say during the 5 minutes following the last shootings, on an arterial catheter) partial pressure of carbon dioxide in arterial blood (PaCO2 – identical sampling procedure as for PAO2)

### III.2.a. Phase IIa

[figure not shown]

#### ✓ Primary objective

To estimate :

- **Accuracy of shootings** on a precise area (step 1) then on a zone to be spared (step 2),  
 ↳ THROUGH: both the distance between the hurt epicentre generated by hifu and a mark (step 1) and between the hurt limit and a vessel border previously marked (step 2). These sizes will be measured in mm during anatomopathological exam.

#### ✓ Secondary objectives

To estimate :

- **Safety** using the MD,  
 ↳ Through: No evidence of hurt on peripheral tissues (Glisson capsule on the opposite side of the HIFU shootings entrance area, retro-peritoneal, retro-hepatic tissues and diaphragm).  
 NB: it is possible that the Glisson capsule ultrasound hurts on the entrance area that will be notified but not considered as a failure.
- HIFU shootings **tolerance**,  
 ↳ Through: Ability to keep vital signs stable (hemodynamic, respiratory, body temperature) during shooting phase and the following 5 minutes.
- **Correlation between hurt perioperative echographic and postoperative macroscopic**, measures,  
 ↳ Through: hurt dimensions comparison (diameters, depth, volume, etc. – in mm), blind-measured, with echography in a first time and in a second time, right after the resection, in anatomopathology.

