### I.3. Development of a toric hifu transducer for treatment of CLM

Cf. biblio (23;24)

[figure not shown]

Figure 1 : HIFU probe.

A perioperative ultrasound medical probe in treatment of CLM with HIFU has been developed and received at a preclinical phase in a porcine model. 7 cm^3 large (20 mm of diameter and 25 mm of long axis) unitary conical resections were done in 40 seconds with a crossed toric transducer which is an efficient result considering the time consumed and the volume treated. A hole in the middle of the medical device (MD) enables to add an echographic probe to localize and control liver metastases treatment. Characteristics of the generated hurts were studied on the models and in *in vitro* and *in vivo* preclinical studies.

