#### I.3.a. Preclinical study of HIFU treatment feasibility: analysis of a single hurt and strategies to extend necrosis

Cf. biblio (25;26)

[figure not shown]

Figure 2: (a) Elementary HIFU hurt generated in 40 seconds  
(b) Echographic aspect of elementary HIFU hurt.

One of the most important things, concerning the CLM treatment, is the accuracy of targeting. In standard surgery or with a therapy using physical agents (radiofrequency, cryotherapy) the treatment is considered properly done when a tumor is killed with negative geometrical margins. The elementary hurt generated by the toric HIFU transducer in treatment of CLM was thoroughly studied in preclinical phase *in vivo* in pig liver. Its geometrical features (Figure 2a) and the absence of cooling effect on perfusion are really relevant to cure CLM taking into account its rich vascularization. The perioperative manual use of toric HIFU transducer prototype gave accurate localized treatment in liver, thanks to the echographic guidance provided by the combined probe. Since both localization and necrosis in liver tissues were controlled, the proposed HIFU treatment seemed to be more convenient. The hurts are homogenous and have, microscopically or macroscopically, well defined borders.

Generated hurts are easily visible on echographic pictures (Figure 2b) which makes possible to place side by side several elementary cone-shaped hurts to extend the size of the generated necrosis (Figure 3). The treatment is non-invasive to the organ and is well tolerated.

[figure not shown]

Figure 3: Juxtaposition of 6 elementary hurts

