#### IV.3.c. Phase IIa

|                                                                                                                                                                                                                  | INCLUSION | PERIOPERATIVE            | POSTOPERATIVE                                        | 30 JOURS POST OPERATION |
|------------------------------------------------------------------------------------------------------------------------------------------------------------------------------------------------------------------|-----------|--------------------------|------------------------------------------------------|-------------------------|
|  DISTANCE BETWEEN 

• HURT EPICENTRE / MARK (STEP 1)

• HURT LIMITS AND MARKED VESSEL BORDERS (STEP 2)

                              |           |                          | 
 |                         |
|  CORRELATION BETWEEN HURT MEASURES TROUGH 

• ECHOGRAPHY COUPLED TO THE MD

• ANATOMOPATHOLOGICAL ANALYSIS RIGH AFTER THE OPERATION

 |           |  |                              |                         |

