## **VI.3. Data analysis**

Data analysis will be mainly descriptive. Qualitative data will be described by their frequency distribution and associated percentage with a 95 % confidence interval. Quantitative data will be described by the number of observations, mean, standard deviation, median, minimum and maximum values.

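### The Phase IIa comparison of echographic and pathological lesion size is named a correlation; agreement in mm is the quantity that answers the question (minor)

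*Protocol*

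**What the plan says.** Among the Phase IIa secondary objectives (Protocol III.2.a) is "Correlation between hurt perioperative echographic and postoperative macroscopic" measures of the HIFU lesion, which the protocol calls a hurt. The line stating how the objective is assessed reads "hurt dimensions comparison (diameters, depth, volume, etc. – in mm), blind-measured, with echography in a first time", followed by a second measurement in pathology straight after resection. The Phase IIa assessment table (IV.3.c) uses the same term: "CORRELATION BETWEEN HURT MEASURES TROUGH" the echograph coupled to the device and the pathological analysis.

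No coefficient, test or target value is given for this objective. Section VI.3 says "Data analysis will be mainly descriptive" and that "Quantitative data will be described by the number of observations, mean, standard deviation, median, minimum and maximum values". It does not say whether this applies to each measure or to the paired difference, and no agreement summary is named.

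On lesion size, I.3 gives one nominal figure from the pig model, "20 mm of diameter and 25 mm of long axis", for an elementary lesion. On depth, the step 1 shooting process (IV.2.c) sets four target positions: the surface, then 40, 20 and 60 mm, each depth with a tolerance of 5 mm.

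**The concern.** The aim is to learn whether the size read on ultrasound during surgery matches the size found in the specimen. That is a question about error in mm. The named quantity, correlation, measures something else in two respects.

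- **It does not see systematic error.** If echography reads every lesion too large or too small by a fixed amount, r is the same as with no error.
- **It depends on the spread of true values.** For the same measurement quality, r is low when lesions are alike and high when they differ widely.

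So r can mislead in either direction here. If elementary lesions are of similar size, as a single nominal size makes plausible, r for diameter could be low although the methods agree closely. If depth means position in the liver, the design spreads it over about 60 mm, and r would be high even with poor measurement.

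Echography guides the juxtaposition of shots in Phase IIb. At the end of Phase IIa the Steering Committee reviews all the data and settles the Phase IIb methodology in more detail (VI.1.b). A result in mm can be used in that review; a correlation is hard to interpret there.

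**Working it through.** **The plan's own figure.** The only numerical justification for Phase IIa (VI.1.b) is a 90% chance of seeing at least one inaccurate patient at true rates of 54% (n = 3) and 32% (n = 6). It reproduces: 1 − 0.46³ = 0.903 and 1 − 0.68⁶ = 0.901. It does not size this objective, for which the protocol gives no figure.

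**Inputs from the protocol.** 6 to 12 patients (VI.1.b) with 2 to 4 lesions each (IV.2.c), so 6 × 2 = 12 to 12 × 4 = 48 lesions, clustered in patients. Step 1 target depths are 0 (surface), 20, 40 and 60 mm.

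**Assumptions.** The protocol gives neither the between-lesion SD (sb) nor the measurement SD (se), so both are assumed and varied. Both methods are given the same se and independent errors.

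**Formulas.**
- r = sb² / (sb² + se²)
- 95% limits of agreement = bias ± 1.96 × √2 × se
- Lin's concordance = 2sb² / [2(sb² + se²) + bias²]

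**Effect of spread.** With se = 1 mm and no bias, the limits of agreement are ±1.96 × 1.414 × 1 = ±2.8 mm in every row.

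| sb (mm) | r | Limits of agreement (mm) |
|---|---|---|
| 0.5 | 0.25/1.25 = 0.20 | ±2.8 |
| 1 | 1/2 = 0.50 | ±2.8 |
| 2 | 4/5 = 0.80 | ±2.8 |
| 5 | 25/26 = 0.96 | ±2.8 |

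A modest spread need not give a low r: with sb = 2 and se = 0.5 mm, r = 4/4.25 = 0.94.

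**Effect of bias.** Add a constant 5 mm error, a size chosen to match the trial's own 5 mm accuracy threshold, with se = 1 mm. The limits become 5 ± 2.8, that is 2.2 to 7.8 mm.
- sb = 5: r stays at 0.96; concordance falls from 0.96 to 50/(52 + 25) = 0.65.
- sb = 1: r stays at 0.50; concordance falls from 0.50 to 2/(4 + 25) = 0.07.

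**Depth, if it means position.** Targets of 0, 20, 40 and 60 mm have mean 30 and variance (900 + 100 + 100 + 900)/4 = 500, so SD 22.4 mm. With a measurement SD as large as 5 mm, r = 500/525 = 0.95, although the limits of agreement are ±1.96 × 1.414 × 5 = ±13.9 mm.

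**Precision.** Treating lesions as independent, which is optimistic, a true r of 0.50 has a Fisher-z 95% CI of −0.10 to 0.83 with 12 lesions and 0.25 to 0.69 with 48. Under the same assumptions (se = 1 mm, SD of the difference 1.41 mm), the half-width for the mean difference is 1.96 × 1.41/√12 = 0.8 mm or 1.96 × 1.41/√48 = 0.4 mm.

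**The case against.** The strongest reply is that the protocol never commits to a correlation coefficient. The explanatory line describes a blinded comparison of dimensions in mm, so the heading word may simply be loose. The choice of statistic for a descriptive secondary objective can properly be left to an analysis plan, which is not shown. The mean and SD listed in VI.3, if applied to the paired difference, would give the bias and the limits of agreement. Most of this stands. It rules out treating the absence of a named agreement method as a gap in itself, and it rules out saying that VI.3 cannot yield the paired error. It does not remove the point: two places name correlation as the quantity, none names the paired difference, and an analysis written faithfully to the objective would report r.

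Three stronger readings are tempting and are not supported.

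- **That r is bound to mislead because lesions are nearly constant in size.** The 20 × 25 mm figure is one nominal size from the pig model; no between-lesion SD is given for pig or human. The remark "The hurts are homogenous and have, microscopically or macroscopically, well defined borders" more naturally describes the texture and edges of a lesion than equal size across lesions.
- **That an echographic under-reading would consume the 5 mm margin of Phase IIb.** An error on a whole diameter is not comparable with a margin on one side. If echography reads too small, the true lesion is larger than it appears, which tends to widen the real margin. Phase IIb success is in any case judged by pathology (III.2.b).
- **That a trial decision rests on this objective.** The Phase IIa continuation rules (VI.1.b) use distances to the mark or vessel, which III.2.a has measured in pathology.

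**Conclusion.** The point holds in a limited form. The objective names a quantity that does not measure what its own explanatory line sets out to compare. Reported alone, r could be too low for diameters and too high for depth, and it would not show a constant bias. Identical limits of ±2.8 mm go with r = 0.50 or 0.96, depending only on the assumed spread between lesions.

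The sizes shown are illustrations. They rest on assumed SDs, equal measurement error in both methods and independent errors; the depth result also requires that depth means position. The invariance of r to a constant bias needs none of these assumptions.

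The impact is minor. This is a secondary, descriptive objective that gates no continuation rule. Its practical use is in the Steering Committee's review before Phase IIb.

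**What to change.** In III.2.a and in the IV.3.c table, replace *correlation* with *agreement*. State that for each dimension (diameters, depth, volume) the analysis reports the mean paired difference, echography minus pathology, with its 95% CI and the 95% limits of agreement (Bland-Altman). The method should allow for 2 to 4 lesions per patient, for example with a patient random effect on the differences. Say whether depth means the extent of the lesion or its position in the liver. The correlation coefficient may stay as a descriptive extra.

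The blinded paired measurements are already planned, so the change adds no patients, visits or measurements. It costs a wording change in two places and a different summary of the same data.

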### III.2.b. Phase IIb

[figure not shown]

#### ✓ Primary objective

To estimate :

- Possibility, by **juxtaposing elementary HIFU hurts in metastases** to be resected, to generate global hurts containing metastases and guaranteeing sufficient safety margin in healthy liver.  
↳ through :
  - 1) Possibility of number of  $\leq 15$  shootings,
  - 2) The hifu hurt generated must encompass the metastasis and guarantee a safety margin  $\geq 5$  mm from any point (anatomopathological analysis).

#### ✓ Secondary objectives

To estimate :

- **Safety** using the MD,  
↳ Through: No evidence of hurt on peripheral tissues (Glisson capsule on the opposite side of the HIFU shootings entrance area, retro-peritoneal, retro-hepatic tissues and diaphragm).  
NB: it is possible that the Glisson capsule ultrasound hurts on the entrance area that will be notified but not considered as a failure
- HIFU shootings **tolerance**,  
↳ Through: Ability to keep vital signs stable (hemodynamic, respiratory, body temperature) during shooting phase and the following 5 minutes.

## **IV. Methods**

---

### **IV.1. Population**

Patients complying with the following criteria:

#### **IV.1.a. Inclusion criteria**

- 18 years old or more patient,
- Affected of hepatic metastasis of a colorectal cancer,
- Who must undergo a hepatectomy by laparotomy with the aim of the resection of hepatic metastasis,
- ECOG performance status (PS) = 1,
- Mandatory affiliation to a health security insurance,
- Written informed consent.

#### **IV.1.b. Non-inclusion criteria**

- Having already undergone a major hepatic surgery (more than three segments) or biliary major (context of major iterative hepatic surgery),
- Having already undergone a major abdominal surgery with the exception of a colorectal surgery for the treatment of its primitive tumor (the surgery of the gall-bladder by laparoscopy for the deadline upper to 6 months do not constitute a criterion of not inclusion),
- Unable to be followed during the duration of the study,
- Pregnant or breast-feeding woman (a pregnancy test must be negative at the time of the inclusion in the study for the women in age to procreate; a method of reliable contraception must be used during the duration of the study).

#### **IV.1.c. Specific inclusion criteria related to phase IIb**

- Having one or more liver metastasi(e)s  $\leq 2$  cm, to be resected by hepatectomy

## **IV.2. Study procedure**

### **IV.2.a. Prerequisites**

The investigator team (investigator surgeon and National Certified Nurse Operating Room (CNOR)) that may act for the present study will have been taught principles of use of the MD by the qualified staff of the EDAP society, prior to the study start.

### **IV.2.b. Inclusion**

The patients will be included during the surgery preliminary visit, by the surgeon (during the month preceding the operation). Once an eligible patient is identified, the investigator will inform him or her about the study, and will give him or her a written informed consent to be signed.

### **IV.2.c. Surgical procedures**

Once liver fully freed and indication of liver resection checked, prior to undertake any specific procedure regarding liver resection, the investigator surgeon will perform the shootings on the dedicated part of the liver.

#### **✓ Anaesthesia procedure**

A standardized anaesthesia procedure will be defined for all patients included in the study.

Shootings will start only once full sedation is achieved. Except in vital emergency cases, no anaesthesia parameter will be modified during the evaluation phase (from first hurt targeting until 5 minutes after the last hurt).

#### **✓ Initialization of the MD and probe preparation**

The initialization of the MD in the operating room and the probe preparation will be done by previously trained CNOR, in parallel to the operation and as far as possible without consequence on the surgical procedure duration.

The whole echographic imaging will be recorded on a DVD.

#### **✓ Patient's preparation**

Vascular access will be given by a central venous catheter and an arterial catheter (procedure not related to the study). Protection compresses will be put under the targeted area to limit risks of ultrasound propagation, and hurt of any nearby organs. Abdominal cavity will be filled with a 37°C saline solution to improve the acoustic transmission between the HIFU transducer and liver. The HIFU probe will be in contact with the liver surface through an ultrasound coupling liquid. From the user interface and with the help of the combined echographic probe, the target of treatment will be defined.

NB: In order to limit as far as possible risks to damage nearby organs, shootings axis will not point towards noble intra abdominal organs.

#### **✓ Shootings process**

##### **⇒ Phase I**

The shootings will concern the healthy liver to remove, distant to the important vascular structures and metastases. Two HIFU shootings will be made on each patient:

- One hurt on the surface starting from the Glisson capsule and extending to subjacent hepatic parenchyma.
- One hurt at given depth, at least 10 mm deeper than the hurt done on the surface

NB: The shooting depth will be determined for each patient at the beginning of the operation, considering preoperative exams (scans, etc.), size and location of the liver part to be resected and physical structure of the patient.

⇒ **Phase IIa**

The shootings will concern healthy liver to be resected, distant (step 1) then close (step 2) to the important vascular structures of the liver. Several shootings HIFU will be made on each patient (ideally 4 hurts, minimum 2 hurts)

Step 1

Each mark will be spotted by a stationary mark set at a given depth (1st hurt on liver surface, 2nd hurt at depth of  $40 \pm 5$  mm, 3rd hurt at  $20 \pm 5$  mm, 4th hurt at  $60 \pm 5$  mm). Shootings will be performed by superimposing the theoretical hurt epicentre and the mark (the mark will have to be included in the generated hurt)

Step 2

Vascular structures will be colored in Patent Blue or Methylene Blue and will work as a mark. Shootings will be performed by positioning the closest theoretical hurt limits to a vessel at a distance of 5 to 10 mm from the vessel border.

⇒ **Phase IIb**

Shootings will concern small metastases ( $\leq 20$  mm) and peri lesional healthy liver. They will be juxtaposed on multiple plans in order to generate a large hurt containing the metastasis targeted and guaranteeing a sufficient safety margin in healthy liver. Several metastases can be treated in the same patient

✓ **Immediate following of the intervention**

The whole abdominal cavity will be explored to detect possible adverse effects, especially burns, involving adjacent organs to liver.

Once HIFU delivered the hepatectomy procedure will be totally identical to the one that would have been done if patient would not have received HIFU shootings.

The anatomopathological analysis will include, in addition, an analysis of each of the HIFU hurts.

